## Abstract

**Background:**

Only one in four people with eating disorders seeks treatment, and of those who do seek treatment, 20% go on to experience a chronic course. Early intervention has been associated with better prognosis, with those seeking specialised intervention in the early stages of their illness more than twice as likely to achieve remission. Current screening measures typically require expert administration and are rarely validated across a spectrum of DSM-5 eating disorder presentations or for online use. In light of COVID-19 and increasing reliance on telehealth technologies in the intervention and delivery of mental health services, online assessments suitable for self-referral are likely to be the first step to seeking care. InsideOut Institute has developed a 6-item online screening tool for the purposes of identifying eating disorder risk and symptomatology, aimed specifically at increasing help-seeking behaviour in subsyndromal and early presentations.

**Methods:**

This study investigates the reliability and validity of the InsideOut Institute Screener (IOI-S), using a cross-sectional survey research design. Participants aged 14 and over will complete an extensive baseline survey battery for evaluation. 50% of participants will be randomly selected for one follow-up re-test of the IOI-S only, 2 weeks post initial testing. The IOI-S will be analysed for statistical reliability on two parameters: internal consistency and test re-test reliability, and for statistical validity on four parameters: concurrent validity, sensitivity and specificity, convergent and discriminant validity.

**Discussion:**

The rapid and ongoing shift to digital intervention has highlighted gaps and opportunities in our pathways to care. Adequate screening for eating disorders is a major gap. This study aims to validate an online screening tool for use in telehealth early intervention, designed for users seeking information for a suspected eating disorder. The screener meets those at risk ‘where they are’ (i.e. online) and may improve timely referrals to relevant services. This is of particular salience as face-to-face healthcare and traditional frontline interventions are disrupted, and we are challenged to re-design our practices to deliver diagnostic and treatment services in highly adaptive digital contexts.

## Plain English summary

Early intervention greatly improves treatment outcome, however currently only 1 in 4 people with an eating disorder seeks treatment. Current screening measures are typically designed to identify traditional cases of Anorexia and Bulimia Nervosa rather than address a spectrum of eating disorder behaviour and are rarely validated for online use. Adequate screening designed to encourage help-seeking behaviour is needed. Given 84% of Australians now seek healthcare information online before going anywhere else, and with a rapid COVID-19 driven shift to digital healthcare and intervention, novel online screening tools designed to identify broad eating disorder risk and symptomatology may become the first step to seeking care. This study aims to validate a 6-item online screening tool developed by the InsideOut Institute for Eating Disorders at the University of Sydney in a diverse population of people aged 14 and over. It is designed to ‘start a conversation’ so that it may be used to encourage help-seeking behaviour and improve timely referrals to relevant services (digital or otherwise).

## Background

Eating Disorders (ED), marked by persistent disturbed eating behaviour and negative psychological affect, are complex psychiatric conditions associated with life-threatening physical complications [1] and high concurrent mood disorders [2, 3]. Anorexia (AN) and Bulimia Nervosa (BN) alone cause 1.9 million disability-adjusted life years globally [4] and cost the Australian economy $69.7 billion per year [5]. Despite this, only one in four people with EDs seek treatment [6], and of those who seek treatment, 20 % will become chronic [7]. Elevated mortality rates and relatively poor treatment outcomes may in part be attributable to a paucity in help-seeking and the frequent delay between illness onset and intervention – a factor known to heavily influence prognosis [8, 9].

Early intervention is paramount to improved treatment outcome [10, 11], however is frequently impeded by mental health illiteracy, self-stigma and shame [12]. Eating disorder stereotypes exacerbate ambivalence towards treatment seeking [13] and contribute to the ego-syntonic nature of the illness, where people can be stuck between the pre-contemplation (denial) and contemplation (awareness with resistance) stages as described by Prochaska’s trans-theoretical model of change [14]. This ambivalence may be compounded by cultural normalisation of dietary and exercise excess, contributing to confusion around experiences of pathology and distress [15].

Screening tools are regularly used to triage medical and psychological risk in healthcare settings and have been shown to be effective in early identification, often triggering referral and further assessment where results suggest a condition may be present [16]. They may have superior utility over long form diagnostic tools in the crucial pre-contemplative stage of an eating disorder, mitigating the challenges clients frequently face in being properly identified by time-poor primary healthcare physicians, many of whom lack the expertise or feel ill-equipped to deliver complex eating disorder assessments [17, 18] such as the gold standard Eating Disorder Examination Questionnaire [19, 20].

A number of screener questionnaires have been validated for use in eating disorders. These include the widely used 5-item Sick, Control, One Stone, Fat, Food (SCOFF) questionnaire (Morgan, Reid & Lacey, [21]) and the 5-item Eating Disorder Screen for Primary Care (ESP) (Cotton, Ball & Robinson, [22]). The SCOFF is brief and has demonstrated good internal consistency and concurrent validity with the EDE-Q, however, shows limited evidence identifying disordered behaviour beyond traditional presentations of AN and BN [23]. Additionally, language may assume acceptance of an eating disorder diagnosis, thus may not be useful in the prodromal phase of the illness. The SCOFF has attracted criticism for its use of confronting behaviour-based questions (e.g. ‘Do you make yourself sick?’, ‘Have you lost more than one stone?’) [23]. These types of questions have been found to be prone to denial or distortion on face-to-face assessment [24]. Moreover, the screener has limited specificity—the authors agreed maximising sensitivity was paramount given the morbidity and mortality associated with eating disorders and the consequences of a false negative result, thus reducing the cut-off from three positive answers to two [21]_._ Importantly, as with most existing screeners, the SCOFF is validated for in-person use only, and thus assumes a person is already in the care of a healthcare professional at the time of taking the test.

The Eating Disorder Screen for Primary Care is more sensitive but less specific than SCOFF at detecting eating disorders [25]. It employs more sympathetic language and includes questions about personal and family history of eating disorder diagnoses, however the latter has been found to have no predictive strength and is dropped from analyses in many cases [25]. The ESP has not been widely circulated or validated.

Several short forms of the EDE-Q, including the EDE-QS (Gideon et al., [26]) (12 items), the EDE-Q7 (Grilo, Henderon, Bell & Crosby, [27]) and the EDE-Q8 (Kliem et al., [28]) have been conceived and psychometrically validated across populations, demonstrating good sensitivity and internal consistency and adequately correlating with the original EDE-Q. However, all utilise the original items, derived from previous iterations of the DSM and prior to the inclusion of diagnostic categories Binge Eating Disorder (BED), Avoidant Restrictive Food Intake Disorder (ARFID), Other Specified Feeding or Eating Disorder (OSFED) and Atypical AN, and again, are not specifically designed for online use.

To our knowledge, there have been few intermediary measures and novel screening tools developed since the 2013 revision of the DSM (5) despite changes to existing diagnostic categories and the inclusion of a BED diagnosis. Further, existing diagnostic and screening measures are typically validated to discriminate between healthy and ill, rather than using a continuum to identify those showing early symptomatology/risk [29]. One recent exception is the Stanford-Washington University Eating Disorder screen (SWED) (Graham et al., [30]) which assigns a risk threshold and has been validated for online use [30, 31]. However, this questionnaire is 17 items long and has been primarily validated in college age females. Given the prognostic implications of early intervention, there is evidenced need to expand on current validated screeners for diverse populations, and to do so in a way that reflects modern-day healthcare and the move to online health information-seeking [32].

Healthcare is experiencing a paradigmatic shift from medical paternalism to autonomous patient-centred care [33] with people increasingly turning to internet technologies for support and advice [34]. Eighty-four percent of Australians log on to the internet to search healthcare information before going anywhere else [35]. The most at-risk population for eating disorders, young people, are significantly more likely to seek initial information online than to visit their GP [36]. The occasion of the COVID-19 global pandemic has driven a sudden shift to online healthcare delivery [37], alongside increased rates of mental health complaints and worsening anxiety and depression [38, 39]. Those suffering from eating disorders are particularly vulnerable during times of food insecurity, with lack of access to “safe” foods combined with erratic food distribution causing a ‘feast or famine’ pattern defined by hoarding, restriction, bingeing and compensation [40, 41]. There is evident emergent need, then, for novel online risk-assessments and screening options suitable for self-referral, where the burden of mental health is increasing while face-to-face access to physicians is curtailed by social distancing measures [42, 43]. New screening tools should address the semantic and methodological limitations of present standardised measures and be validated for online use across the spectrum of eating disorders as defined by the DSM-5 (including presentations of BED, ARFID and OSFED). They may be more acceptable and less susceptible to denial and distortion by employing non-confrontational language [24]. To this end, InsideOut Institute for Eating Disorders (IOI) within the Boden Collaboration for Obesity, Nutrition, Exercise and Eating Disorders, The University of Sydney, conceptualised a short, 6-item online screening tool, the InsideOut Institute Screener (IOI-S, [44]) to assess for eating disorder symptomatology/risk using non-intrusive, sensitive language designed to ‘start a conversation.’

This study aims to psychometrically validate the IOI online screener so that it may be used reliably as an adjunct or alternative to existing screening measures and/or for referral purposes, encouraging online users who may otherwise have delayed seeking professional help to do so with self-governance and autonomy.

## Methods/design

### Participants

Approximately 250 participants will be recruited into the study. They will be aged 14 and over, of all genders, and divided into two groups – clinical and non-clinical. Clinical status will be determined post-testing using EDE-Q cut-off scores. We aim to recruit across all DSM 5 diagnostic categories for eating disorders.

Participants will be recruited in two ways:
*Amazon’s Mechanical Turk (MTurk):* ‘MTurk’ is a global internet crowdsourcing service used frequently in academic research to recruit a broad base of willing research participants who are compensated for completing surveys, questionnaires and tasks as assigned by the researcher [45]. MTurk does not permit people under 18 to use its service: thus, it will be used to recruit adults aged 18+ only, both clinical and non-clinical. Participants will be able to sign up from anywhere in the world, deeming it an international cohort. They will be reimbursed according to MTurk recommendations.*Community:* Participants will be recruited via online advertisements on health websites and social media channels/paper advertisements. Advertisements will be aimed at individuals who self-report an eating disorder diagnosis, though those without an eating disorder are also welcome to participate, and all will go into the draw to win a Westfield gift card. We are specifically looking to recruit adolescents via this method, due to MTurk’s restriction on underage participants, however adults will also be targeted.

The use of two methods of recruitment aims to increase generalisability across age, ethnicity, gender and Body Mass Index (all of which will be reported) – this is significant due to the broad-reaching nature of the internet and the importance of validating the questionnaire across populations.

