#### Criterion validity

The degree to which the results on the IOI-S are able to predict an outcome on established measures of eating disorder symptomatology (concurrent validity) [63] will be assessed as concordance between the IOI-S, the EDE-Q, and the SCOFF using a Spearman’s product moment correlation. Following, an Area Under Curve (AUC) analysis of Receiver Operating Characteristic (ROC) curve will be performed as analysis of IOI-S sensitivity and specificity threshold where a high sensitivity indicates accurate identification of true positive cases and high specificity indicates accurate identification of true negative cases [64]. Area Under Curve dictates the probability of identifying true positives or negatives by chance, where a value of 0.50 would suggest the measure is no more effective than guessing [65]. AUC threshold will be set at > 0.70 with a 95% confidence interval.

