#### Construct validity

Convergent validity, or the degree to which the IOI-S correlates with eating disorder constructs and variables on both the EDE-Q and the SCOFF [66] will be measured with a correlation coefficient threshold set at *r >* 0.70. A correlation coefficient will also be determined for discriminant validity between the IOI-S and MC-SDS/CSD-S. A correlation coefficient of +/− 0.70 indicates a strong linear relationship between two variables [67].

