## Discussion

The internet is changing the way we seek and deliver healthcare, and current circumstances brought on by the COVID-19 global pandemic have intensified the need for validated online interventions and services, particularly where appropriate intervention at first point of contact is shown to be of fundamental gain to outcome. The primary outcome of this study is to establish if the Inside Out Institute Screener is a statistically reliable, valid and accurate online measure of eating disorder risk and symptomatology in those aged 14 and over so that it can be reliably used by those seeking information for a suspected eating disorder. The development of the tool was predicated on the understanding people now pursue support and information for healthcare concerns on the internet before presenting anywhere else, and the opportunity this presents to inform and encourage help-seeking behaviour in a population largely going undetected in primary healthcare [18]. Although primarily intended for personal use and potential self-referral, the screener is further designed to accurately identify clinical status and thus has the potential to be used in a clinical setting to distinguish true cases from non-cases, with treatment elucidated on that basis.

Questionnaires used in the field of eating disorders have mostly not been validated for online use. Instead, scores on each measure and respective community/clinical norms are derived from paper administration. This is often performed in conjunction with a trained clinician, which as stated, can confound results due to the nature of these types of questions being prone to denial and distortion on face-to-face assessment. Thus, lack of available norms for online administration may impact the findings. However, inclusion of the current gold-standard screening tools against which to validate was determined to be of necessary importance. Additionally, as all surveys are being delivered online in this instance, any effect due to test condition will be homogenous across the survey sample.

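### Community recruitment targets people with a self-reported diagnosis, but the AUC and r criteria are not tied to the undiagnosed information-seekers whom the conclusion concerns

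*Protocol article*

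**What the plan says.** **Who is recruited.** There are two routes (Protocol article, Participants). For the community route, "Advertisements will be aimed at individuals who self-report an eating disorder diagnosis", with the addition that "those without an eating disorder are also welcome to participate". For MTurk, "it will be used to recruit adults aged 18+ only, both clinical and non-clinical". No quota or expected share of diagnosed participants is given.

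**How a case is defined.** "Clinical status will be determined post-testing using EDE-Q cut-off scores". Neither the self-reported diagnosis nor the recruitment route defines a case.

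**Whom the tool is for.** The Abstract describes it as "aimed specifically at increasing help-seeking behaviour in subsyndromal and early presentations". The Discussion gives the primary outcome as establishing reliability, validity and accuracy from age 14 upwards "so that it can be reliably used by those seeking information for a suspected eating disorder". The description of the IOI-S under Baseline package says the six items were chosen to assess pathology and risk in a non-clinical population.

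**What counts as success.** Under Criterion validity: "AUC threshold will be set at > 0.70 with a 95% confidence interval". Under Construct validity, convergence with the EDE-Q and SCOFF "will be measured with a correlation coefficient threshold set at" r > 0.70. Neither section names the participants in whom the threshold must be met.

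**The concern.** Someone seeking information about a suspected disorder has symptoms or doubts but usually no diagnosis. The community advertisements look for people who already report one. If those people sit higher on both the IOI-S and the EDE-Q, the sample spreads out on both scales. That raises the correlation between the scales. It also raises the AUC, because many of the EDE-Q cases are then high scorers who are easy to tell apart from non-cases. Neither gain shows that the screener separates cases from non-cases among people without a diagnosis.

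At stake is the main conclusion. Followed as written, the study could meet both criteria overall while the same statistics fall below 0.70 in the people whom the Discussion names.

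**Working it through.** The plan contains no figure for this effect, so there is none to reproduce. The check asks how far the overall statistics can lie above those in undiagnosed participants.

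**Inputs from the protocol:** thresholds r > 0.70 and AUC > 0.70; cases defined by an EDE-Q cut-off; total of about 250.

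**Assumed, because the documents do not give them:** p, the share with a self-reported diagnosis (0.3 or 0.5); d, the mean difference between diagnosed and undiagnosed in within-group SD, equal on both scales (1.5 to 2.5); r_w, the correlation within each group (0 to 0.4); the EDE-Q cut-off, 1.0 or 1.5 SD above the undiagnosed mean; normal scores within groups. Convergence is worked for the EDE-Q only, not the SCOFF.

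**Overall correlation.** With a = p(1 − p)d², overall r = (r_w + a)/(1 + a).

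- p = 0.5, d = 2.5, r_w = 0.3: a = 0.25 × 6.25 = 1.5625, so r = 1.8625/2.5625 = 0.73.
- p = 0.5, d = 2, r_w = 0.3: a = 1, so r = 1.3/2 = 0.65.
- p = 0.3, d = 2.5, r_w = 0.3: a = 0.21 × 6.25 = 1.3125, so r = 1.6125/2.3125 = 0.70 (0.697, just short).

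**Can the group difference alone reach r = 0.70?** With r_w = 0 this needs a/(1 + a) = 0.70, so a = 2.33. That gives d = √(2.33/0.25) = 3.1 at p = 0.5 and d = √(2.33/0.21) = 3.3 at p = 0.3. At 2 to 2.5 SD some real within-group correlation is also needed: 0.40 to 0.23 at p = 0.5, and 0.45 to 0.31 at p = 0.3.

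**AUC against an EDE-Q cut-off.** This was found by simulation. Cases are set by the EDE-Q score, so diagnosed people below the cut-off count as non-cases. Ranges cover the two cut-offs.

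| p | d | r_w | Overall r | Overall AUC | Undiagnosed r | Undiagnosed AUC |
|---|---|---|---|---|---|---|
| 0.5 | 2.5 | 0.3 | 0.73 | 0.90 | 0.30 | 0.66–0.68 |
| 0.5 | 2 | 0.3 | 0.65 | 0.84–0.85 | 0.30 | 0.66–0.67 |
| 0.5 | 2 | 0 | 0.50 | 0.78–0.79 | 0 | 0.50 |
| 0.5 | 2 | 0.4 | 0.70 | 0.86–0.87 | 0.40 | 0.71–0.73 |
| 0.3 | 2.5 | 0.3 | 0.70 | 0.87–0.90 | 0.30 | 0.65–0.67 |
| 0.3 | 1.5 | 0.3 | 0.53 | 0.77–0.79 | 0.30 | 0.66–0.67 |

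In the first row both criteria pass overall and both fail among the undiagnosed. In the third row the AUC criterion passes overall although the screener carries no information among the undiagnosed. In the fourth row the undiagnosed pass the AUC criterion, and r does not exceed 0.70 overall.

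**Precision of a no-diagnosis estimate.** With p = 0.5, 250 × 0.5 = 125 people have no diagnosis. At the 1.0 SD cut-off about 16% of them are cases: 125 × 0.16 = 20, against 105 non-cases. The Hanley–McNeil variance at AUC A = 0.655 uses A² = 0.429, Q1 = 0.655/1.345 = 0.487 and Q2 = 2 × 0.429/1.655 = 0.518. It is [0.226 + 19 × 0.058 + 104 × 0.0894]/(20 × 105) = 10.63/2100 = 0.0051, so the SE is 0.071 and the 95% interval is about ±0.14.

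**The case against.** - **The analysis population is not stated.** The validity sections never say that the routes are pooled. Inclusion/exclusion criteria says the clinical and non-clinical groups are compared, and the power figures under Sample size calculation open on a per-group basis. A reader might infer a decision to pool; the text does not establish one for the correlations. What remains is that an ROC analysis must combine cases and non-cases. The per-group wording also refers to groups split by EDE-Q score, each of which can mix diagnosed and undiagnosed people.
- **The arms are mixed.** A reader might picture known patients set against paid volunteers. The documents do not support that: MTurk takes clinical and non-clinical adults, the community route is open to people without a disorder, and the EDE-Q defines cases. Mixing the arms may shrink the inflation but does not rule it out.
- **Enrichment has a legitimate purpose.** The protocol wants all DSM-5 categories represented, and the Discussion also foresees clinical use in separating cases from non-cases. Targeted advertising helps to find enough cases among about 250 people. This stands, and it is why recruitment need not change.
- **An article omits detail.** Diagnosis status may already be collected, and subgroup tables may sit elsewhere. The point therefore rests on what is printed: whom the advertisements seek, the thresholds, and the claim.
- **The SCOFF remark.** The Background says the SCOFF's language may presuppose accepting a diagnosis. A reader might extend this to screeners in general or to how diagnosed people answer the IOI-S; the text says neither.

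**Conclusion.** The concern holds in limited form. The advertisements seek people with a self-reported diagnosis, the conclusion is about people with a suspected disorder, and the single AUC and r criteria are not tied to the latter. If diagnosed participants score higher on both scales, the overall statistics overstate performance in the intended users.

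The size is uncertain. At p = 0.5, d = 2.5 SD and r_w = 0.3, the overall figures pass (r 0.73, AUC 0.90) while the undiagnosed fail (r 0.30, AUC 0.66 to 0.68). Smaller separations or shares give less inflation, and in many of these settings r > 0.70 is not met overall. The AUC criterion is the more exposed of the two: a 2 SD difference alone carries it past 0.70. It would be wrong to conclude that the group difference alone meets r > 0.70, since that needs a separation of more than about 3 SD. All of this rests on the assumed share, separation, within-group correlation, cut-off and normal model.

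**What to change.** 1. Record current or former eating disorder diagnosis at baseline, if it is not already collected.
2. Report the AUC with its 95% interval, sensitivity and specificity, and convergent r in participants without a diagnosis, and by recruitment arm, beside the overall figures.
3. Base the Discussion's claim about information-seekers on the no-diagnosis estimate, held to the same 0.70 thresholds. If that estimate is too imprecise, limit the conclusion to separating high from low EDE-Q scorers in a mixed sample.

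Recruitment is unchanged. The cost is at most one self-report question and a repeat of planned analyses in subgroups. The downside is fewer cases, wider intervals (about ±0.14 on the AUC in the setting worked above) and probably less favourable estimates.
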